### Literature review

There is moderate-quality evidence that mechanical methods (such as a balloon catheter) are a safe and effective alternative to pharmacological methods to ripen the cervix and induce labour. The Cochrane review on mechanical methods included 17 randomised controlled trials (RCTs) (1894 women) comparing IOL with mechanical methods to PGs [8]. Women undergoing IOL with a balloon catheter had less uterine hyperstimulation (0% vs 5%, risk ratio (RR) 0.16 (0.06–0.39)), and fewer instrumental vaginal births (21% vs 27%, RR 0.79 (0.64–0.98)). Balloon-catheter inductions were associated with more oxytocin usage (75% vs 50%). Both methods had comparable rates of vaginal birth not achieved within 24 h (RR 1.97 (0.43–8.95)), and of caesarean section (26% vs 23%, RR 1.07 (0.91–1.25)).

Diederen et al. performed a meta-analysis of 26 studies (8292 women) who had undergone cervical ripening with a balloon catheter [9]. The most common adverse event was participant pain/discomfort, which occurred in 3 in 1000 participants. This study suggests that the risk of adverse events, such as uterine hyperstimulation, during the period between insertion and expulsion of a balloon catheter in cervical ripening is very low (ranging from 0.0 to 0.26%). The authors concluded that further evaluation and implementation of this procedure in an outpatient setting for low-risk pregnancies was needed.

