### Setting

Ten public hospitals around NZ are currently participating in the OBLIGE trial. These are Auckland, Tauranga, Whakatane, North Shore, Waitakere, Waikato, Wellington, Hawkes Bay, Taranaki, and Hutt Valley Hospitals. These hospitals serve urban, regional, and rural areas, and account for 50% of all women giving birth in NZ [3]. The number of women giving birth per year varies from 1514 in Taranaki to 7557 at North Shore/Waitakere [3].

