### Measured at time of birth

Proportion of participants who had use of oxytocin infusion and at what cervical dilation it started (median score, from 0 to 10)Uterine hyperstimulation (yes/no)Proportion of participants who had use of epidural anaesthesia and at what cervical dilation it was placedClinical diagnosis of chorioamnionitis (yes/no)Proportion of participants who had a clinically significant antepartum haemorrhage after start of IOL – cause, timing, and if associated with abnormal CTGFetal blood sampling (lactate or pH) performed during labour (proportion of participants who had this done) and results (mean measurement)Mode of birth (proportion of participants who had spontaneous vaginal, assisted vaginal or caesarean section)Proportion of participants who had a vaginal birth within 24 h of start of IOLIf caesarean section, reason and at what cervical dilation (mean score, from 0 to 10)Proportion of participants who had failed IOL (defined for the purposes of this study as caesarean section performed at < 4 cm)Uterine rupture (yes/no)Non-cephalic presentation (yes/no)Cord prolapse (yes/no)Stillbirth (yes/no)

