### Sample size calculation

At Auckland Hospital in 2015, the caesarean section rate in women who had undergone IOL (excluding women who had undergone previous caesarean section) was 24.8%, almost all of these women were induced using PGs [16]. In the small trial of outpatient vs inpatient balloon-catheter IOL, the risk of caesarean section rate decreased from 43 to 29% (a relative reduction of 32%) [11]. In order to detect a clinically meaningful change in risk of caesarean section rate from 24.8 to 18.8% (a relative risk reduction of 24%), with 80% power and a two-sided type 1 error of 0.05, we require a sample size of 743 women for each study group. Adding a continuity correction, the total sample size required is 1552 women.

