### Randomisation

On the day of IOL, after confirming eligibility, the clinician will obtain written consent from the participant. Participants will be randomised to one of two study groups, either the outpatient balloon-catheter group or the inpatient PG group, using a centralised, secure, online randomisation website. The randomisation schedule was prepared by the OBLIGE Trial Steering Committee (TSC). Randomisation is stratified by hospital and by parity (nulliparous or multiparous). Allocation is at a 1:1 ratio to outpatient balloon catheter: inpatient PG. The clinician, with support from the research team (if required), will perform the online randomisation, enrol the participant, and allocate the intervention to the participant.

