### Statistical analysis

Baseline demographic and clinical characteristics will be described for each study group. Analyses will follow the principle of intention-to-treat; participants will be analysed according to the assigned intervention group at randomisation. Multivariable models will control for potentially confounding variables and include hospital site and parity. Binary endpoints will be analysed using logistic regression to estimate odds ratios for the intervention. Continuous outcomes will be modelled using generalised linear models to estimate any changes in outcomes between the two interventions. A *p* value of 0.05 will be considered as statistically significant. We recognise that there are a number of secondary outcomes; as they are secondary outcomes we will report *p* values without correction, which would be overly conservative. Missing data will not be imputed.

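### Logistic-regression odds ratios are prescribed for every binary endpoint, including outcomes so rare that an arm may have no events and the odds ratio is then not finite

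*Protocol article*

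**What the plan says.** The protocol article, under Statistical analysis, gives a single rule for binary outcomes: "Binary endpoints will be analysed using logistic regression to estimate odds ratios for the intervention". On covariates it says "Multivariable models will control for potentially confounding variables and include hospital site and parity". The same paragraph sets 0.05 as the significance level and says that secondary outcomes will be reported with uncorrected p values. It does not separate common from rare outcomes, does not name the test behind the p value, and does not say whether site is a fixed or a random effect.

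The binary secondary outcomes include "Uterine rupture (yes/no"), cord prolapse and stillbirth at birth, and maternal intensive care admission before discharge. For the baby they include seizures, encephalopathy and early neonatal death. No expected rates are given for these.

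The design facts that matter are these:
- Setting: "Ten public hospitals around NZ are currently participating in the OBLIGE trial".
- Randomisation: "Randomisation is stratified by hospital and by parity (nulliparous or multiparous"), with 1:1 allocation.
- Sample size calculation: 1552 women in total.

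Secondary hypotheses includes the expectation that the outpatient balloon will not increase adverse events for mother or baby. Harms says that all severe adverse events will be reported in the results paper, without naming a method of comparison.

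**The concern.** A logistic model estimates the treatment effect as a difference in log odds. If one arm has no events, its log odds is minus infinity and maximum likelihood has no finite solution. If neither arm has events, there is nothing to estimate. Software often does not say so clearly: it stops iterating, prints a very large coefficient with a far larger standard error, and reports a Wald p value close to 1.

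The rarest listed outcomes bear on whether the outpatient strategy is safe, and a stated hypothesis is that adverse events do not increase. A p value near 1 produced by numerical failure looks the same as one produced by similar event counts. If the fallback method is chosen only after the counts are known, the choice is also open to the charge of selective reporting.

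**Working it through.** **1. Arm size.** The design is "from 24.8 to 18.8% (a relative risk reduction of 24"%), with 80% power and two-sided 0.05. The pooled proportion is (0.248 + 0.188)/2 = 0.218.

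n = [1.96·√(2·0.218·0.782) + 0.8416·√(0.248·0.752 + 0.188·0.812)]² / 0.06² = 742.2, rounded up to 743 per arm.

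With continuity correction: (743/4)·[1 + √(1 + 4/(743·0.06))]² = 775.98, so 776 per arm and 1552 in total. Both published figures reproduce.

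**2. Chance of an empty arm.** Assume a true risk p, equal in both arms. The chance that one arm has no events is (1 − p)^776. The chance that at least one arm has none is 1 − [1 − (1 − p)^776]². At 0.1%, 0.999^776 = 0.460, and 1 − 0.540² = 0.708.

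The last column comes from 500 simulated trials per rate. The model had arm, parity and ten fixed site effects, with an assumed 60/40 parity split and equal site sizes. Skewed site sizes gave nearly the same values.

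| Assumed risk | Expected events in 1552 | Chance that at least one arm is empty | Median upper/lower ratio of the 95% CI, when finite |
|---|---|---|---|
| 0.05% | 0.8 | 90% | about 260 |
| 0.1% | 1.6 | 71% | about 125 |
| 0.2% | 3.1 | 38% | about 94 |
| 0.3% | 4.7 | 18% | about 51 |
| 0.5% | 7.8 | 4% | about 20 |
| 1% | 15.5 | 0.1% | about 8 |

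The third column includes trials with no events in either arm: 0.460² = 21% at 0.1% and 0.211² = 4% at 0.2%.

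**3. What the software prints.** Take 6 events vs 0 in arms of 776, with arm only in the model. A standard fit stops at a log odds ratio of about −21.7 with standard error about 12,784, so z = −0.0017 and the Wald p is about 0.999. Fisher's exact two-sided p is 2·C(776,6)/C(1552,6) = 2·0.01547 = 0.031. For 39 vs 0 the Wald p is again about 0.999, while Fisher gives 2 × 10⁻¹².

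The likelihood-ratio test does not collapse in this way. For 6 vs 0, G² = 2·[6·ln 2 + 770·ln(770/776) − 1546·ln(1546/1552)] = 8.34 on 1 df, p = 0.004. The p value near 1 is therefore specific to Wald output, but the infinite odds ratio is not.

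**4. Role of the hospital and parity terms.** Step 3 fails with no covariates at all. In the simulations the treatment odds ratio was finite whenever both arms had events. Hospitals without events only made their own coefficients diverge. At 0.2% the adjusted standard error was 1.16, against √(1/1.5 + 1/1.5) = 1.15 for an unadjusted table with 1.5 events per arm.

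**5. Outcomes that are not in trouble.**
- Caesarean section: 776·(0.248 + 0.188) = 338 expected events.
- Hyperstimulation: the Literature review says that balloon women "had less uterine hyperstimulation (0% vs 5"%), with RR 0.16. With 5% under prostaglandin, about 39 events are expected. At 5%·0.16 = 0.8% with the balloon, 776·0.008 = 6.2 are expected, and the chance of none is 0.992^776 = 0.2%.

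**The case against.** **The analysis plan may deal with this.** The article condenses its methods, and handling of sparse outcomes is often left to an analysis plan, which is not shown here. Silence on a fallback would indeed be no finding. But the article is not silent: it states a method for all binary endpoints, and that method cannot deliver for some of those it lists whenever an arm is empty. A sensible analysis plan would have to depart from the published rule.

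**The rates are unknown.** This stands. The size of the problem depends on assumed risks, and at about 1% or above it disappears.

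**Severe events will be reported anyway.** Also true, and it limits the damage. However, the list under Harms omits uterine rupture and seizures, and reporting events does not settle how the arms are compared. With one to three events no method gives an informative comparison. An exact method at least shows that honestly.

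**Stronger readings that do not hold.**
- A reader might infer that ten hospitals and parity in the model cause the failure. They do not (step 4), and the article does not say that site is a fixed effect.
- A reader might take the cited 0% for hyperstimulation, or the 0.0 to 0.26% adverse-event range, to mean that the hyperstimulation odds ratio will not be estimable. The same sentence as the 0% gives RR 0.16, which implies about 6 balloon-arm events. The 0.0 to 0.26% range covers only the time from insertion to expulsion of the balloon. The trial lists this outcome as measured at birth, after possible oxytocin or second-line prostaglandin, and analyses by intention to treat. Even at 0.26%, the chance of no balloon-arm events is 0.9974^776 = 13%.

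**Conclusion.** The point holds for the very rare binary outcomes and only for those. If the true risk is about 0.2% or less in each arm, the prescribed odds ratio has at least a 38% chance of not being finite. When it is finite, its 95% interval spans roughly two orders of magnitude. At 0.3% the chance is 18%, at 0.5% it is 4%, and at 1% it is negligible.

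These figures assume equal risks, full recruitment and complete outcome data. Fewer women analysed would raise them slightly. The misleading p value further assumes default Wald output, because the article names no test.

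It would go too far to say that the safety outcomes in general have no usable estimate. The primary outcome, outcomes near 1% or above, and hyperstimulation at the cited risk ratio are not materially affected. The change should be made because the rule as written could produce a falsely reassuring p value on a stated hypothesis, and correcting it is cheap.

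**What to change.** Amend the Statistical analysis section, or override it expressly in the analysis plan before the data are unblinded:

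- Limit adjusted logistic regression to binary outcomes with enough events, by a numerical threshold fixed in advance. About 10 events in each arm is one option. It would move hyperstimulation, with about 6 expected balloon-arm events, to the sparse route, so the threshold should be chosen with that in mind.
- Below the threshold, report counts by arm and an unadjusted risk difference with an exact or Miettinen-Nurminen 95% CI.
- Take any p value for these outcomes from an exact test.
- If a ratio is wanted, use a Firth-penalised or exact odds ratio.

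The cost is a sentence or two of text, with no effect on sample size, data collection or the primary analysis. The downside is that the rare outcomes are not fully adjusted for the stratification factors, hospital and parity. Little is lost in precision: at 0.2% the adjusted and unadjusted standard errors were 1.16 and 1.15.

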### Cost-effectiveness analysis

Our approach will be to relate costs to outcomes for both arms of the study, allowing for the calculation of ICERs for the primary study outcome – caesarean section rate. In addition, a comparative cost analysis will be conducted to demonstrate the budget impact of wide-scale uptake of the intervention, given that length of stay and complication rates are higher for caesarean section. The approach taken will be to monitor costs as captured through utilisation for mothers and their babies from the point when IOL is initiated until discharge from hospital. Costs will be calculated using NZ Ministry of Health cost weights per event data which will allow for a summative total cost per delivery. Average costs will be compared between the study groups which will allow for the calculation of the net cost of the intervention. The net cost will be related to the primary outcomes of interest which will be then used to calculate ICERs for vaginal births and caesarean sections.

### Data monitoring

The Chair of the Data Safety and Monitoring Committee (DSMC) is a professor of obstetrics, and other members of the Committee are an academic obstetrician and an academic neonatologist (all associated with the University of Auckland). The DSMC defined the serious adverse events (SAEs) to be reported, prior to the start of the trial. The Chair of the TSC is the PI and the Committee includes a multidisciplinary team of researchers. The TSC and DSMC agreed that an interim analysis would be unnecessary.

### Harms

The database has alerts set for any occurrence of a SAE, which is reported to the PI, who informs the Chair of the DSMC. SAEs include: maternal death, maternal admission to intensive care, cord prolapse, stillbirth, neonatal sepsis, neonatal encephalopathy (moderate-severe), and early neonatal death. All severe adverse events will be reported in the publication of trial results.

### Audit

The PI performs an audit of trial conduct every 6 months and reports to the DSMC.

### Confidentiality

Participant’s personal information is collected on paper data forms. Data are entered into the secure online database. In Auckland, the paper forms are directly transferred to the locked office of the PI where they are kept in a locked cupboard. Forms from the other research sites are scanned and emailed to the Trial Manager for data checking, then kept securely in a locked cupboard or office of the local research team. The data will be de-identified prior to data analysis. Electronic data will be maintained in the database for 10 years as per ethics requirements in NZ, and paper forms from all sites will be placed in a secure university storage facility for the same duration.

### Dissemination policy

Results from this trial will be published in an appropriate peer-reviewed obstetrics journal. Authorship will be as per International Committee of Medical Journal Editors (ICMJE) guidelines. Researchers will also present results locally and nationally to other health care professionals. On the Consent Form (CF), participants are asked if they would like to receive a summary of the study results by email; this will be tracked in the database. Results will also be published on a public website www.oblige.auckland.ac.nz

## Discussion

This study has the potential to significantly change IOL practice in NZ and around the world. Paramount to all other outcomes from this study is that a simple intervention, such as a switch to the use of balloon catheters as the default method of IOL, may reduce the risk of caesarean section. Very few obstetric interventions studied in the last decade have resulted in reducing the caesarean section rate. A multi-faceted 2-year intervention in 32 Quebec hospitals managed to significantly reduce the caesarean section rate from 22.5 to 21.8% [19]. A 2-year quality improvement project in 56 California hospitals (the Toolkit Collaborative) found a significant reduction in caesarean section rate among standard nullipara, from 29 to 25% [20]. The OBLIGE trial is powered on the ability to detect a 24% relative reduction in risk of caesarean section, in a subset of women undergoing IOL. The ‘Choosing Wisely’ campaign has been put in place to facilitate wise decisions between service providers and patients about the most appropriate care for them, avoiding unnecessary interventions [21]. This study should provide the evidence to make such recommendations for IOL care provision.

Not only do most women want fewer interventions during childbirth (as long as they and their babies are safe), but women also want choice. If outpatient IOL with a balloon catheter is found to be both clinically effective and safe, then women who require an IOL can have some choice in how and where it will occur.

From a hospital service perspective, if outpatient balloon-catheter IOL is found to be cost-effective, then enabling women to access this method of cervical ripening has the potential to save significant resources in midwifery time, other resources and overall length of hospital stay. Hospitals have a great shortage of midwifery staff; thus, innovative solutions are needed to optimise the wise use of this resource. Moreover, the cost of a balloon catheter is much less than the cost of a single PG dose.

### Trial status

First participant recruited on 25 October 2017; anticipated recruitment completion December 2020; Study Protocol Version 9 dated 12 October 2018.

### Recruitment progress

Based on indications for IOL at Auckland Hospital [16], we estimated that 40% of women would be eligible for this trial. In keeping with previous trials, we estimated that 60% of eligible women would consent to participate. We additionally accounted for 5% drop out between randomisation and collection of primary outcome data.

We reviewed the number of IOLs at the hospital sites that expressed interest in participating in the trial, and the expected participants per annum ranged from 50 (Whakatane) to 870 (Auckland). Based on the assumption that all sites could start recruitment at the same time, we expected the overall study’s recruitment to take about 15 months (100 participants per month).

The first site to start the trial was Auckland Hospital and the first participant was recruited in October 2017. During 2018, seven more hospitals signed research contracts to be involved in OBLIGE, and three in 2019. Monthly recruitment increased from five participants in November 2017 to 41 in May 2019 (see Fig. 2). The total recruitment to date is over 450 participants.

**Fig. 2 Fig2:**
[figure not shown]
Monthly cumulative recruitment by site

Recruitment has been slower than our estimates. On recent audit of three sites, eligibility rate was 40%, as expected. However, the acceptance rate was 25% which is much lower than expected. Based on revised practical estimates, we now anticipate completion of recruitment in December 2020.

## Data Availability

The final trial datasets generated and analysed during the current study will be accessible by the TSC, and to the DSMC on request. The corresponding author will also make the datasets available, on reasonable request, in order to contribute to an individual participant data (IPD) meta-analysis. De-identified trial data will be shared in accordance with the ICMJE data-sharing guidelines.

## Abbreviations

ANZCTR: Australian New Zealand Clinical Trials Registry
ARM: Artificial rupture of membranes
CF: Consent Form
CTG: Cardiotocography
DSMC: Data and Safety Monitoring Committee
HDEC: Health and Disability Ethics Committee
ICER: Incremental cost-effectiveness ratio
ICMJE: International Committee of Medical Journal Editors
IOL: Induction of labour
NPRS: Numeric pain rating scale
NZ: New Zealand
PGs: Prostaglandins
PI: Primary investigator
PIS: Patient Information Sheet
RANZCOG: Royal Australian and New Zealand College of Obstetrics and Gynaecology
RCT: Randomised controlled trial
RR: Risk ratio
SAE: Serious adverse event
TSC: Trial Steering Committee
